## Abstract

**Background:**

Communication, impulse control and motivation can all be affected by Bipolar Disorder (BD) making consistent parenting more difficult than for parents without mental health problems. Children of parents with BD (CPB) are at significantly increased risk of a range of mental health issues including Attention Deficit Hyperactivity Disorder (ADHD), anxiety, depression, substance use, and sleep disorders. Furthermore, CPB are also at elevated risk for BD compared to the general population. This paper describes the rationale and protocol for a pilot randomised controlled trial (RCT) designed to assess the feasibility and acceptability of a new online intervention providing interactive psychoeducational information and parenting support for parents with BD.

**Methods and design:**

This article describes a single-blind randomised controlled trial comparing an Integrated Bipolar Parenting Intervention (IBPI) in addition to treatment as usual (TAU) with TAU alone. Participants will be recruited from across the UK from mental health services and through self-referral. The primary outcome of the study is the feasibility and acceptability of IBPI as indicated by recruitment to target, use of the intervention site, and retention to follow-up. Parents with BD allocated to the IBPI condition will have access to the intervention for 16 weeks. Effect size estimates will be obtained with respect to child behaviour, parenting skills and measures of parental mental health using measures taken at baseline (0), and at 16, 24, 36, and 48 weeks post randomization.

**Discussion:**

This is the first randomised controlled trial of an integrated bipolar disorder parenting intervention. The benefits and challenges of delivering this online intervention, and evaluation using online RCT methodology are discussed.

**Trial registration:**

Current Controlled Trials ISRCTN75279027 Registered 12 August 2013

## Background

Bipolar Disorder (BD), which has a prevalence rate of approximately 1 to 1.5 % [1] is characterised by recurrent periods of high mood (mania) and low mood (depression). Difficulties with work-related performance, financial issues, social/leisure activities and social/family relationships are common [2], though positive experiences of BD have also been identified [3]. Overall, BD tends to have a significant negative impact on the individual, family, and society, with an estimated annual financial cost in England alone of £5.2 billion [4].

Many individuals with mental health problems are also parents. An Australian study estimated that 23 % of children live in families with at least one parent with a mental health illness and 20 % of users of mental health services have dependent children [5]. The Royal College of Psychiatrist’s report ‘Parents as patients: supporting the needs of patients who are parents and their children’ [6] has highlighted the potential impact of parental mental health issues on children, especially severe mental illness, such as bipolar disorder. Parenting can be a particular challenge for parents who are living with bipolar disorder, as there can be difficulties with sleep/wake cycles, impulse control, motivation and communication [7,8] which can impact on their ability to consistently engage in adaptive parenting.

There is now consistent evidence that children of parents with BD (CPB) are vulnerable to a wide range of behavioural and emotional conditions including Attention Deficit Hyperactivity Disorder (ADHD), anxiety, depression, substance use, and sleep disorders, in addition to higher rates of BD compared to the general population [9-11]. However, it is possible that parenting programmes, designed to help parents to encourage desirable behaviour and cope with challenging behaviour in their children may be effective in enhancing the confidence and skills of bipolar parents, and in doing so, can help ameliorate these vulnerabilities. Parenting programmes are delivered in a range of formats from group settings to online and typically build on parenting strengths rather than highlighting weaknesses. There is evidence that such programmes can effectively reduce child problem behaviours including conduct, antisocial behaviour and attention deficit disorders [12-14].

A particular parenting programme (Triple P), developed by one of the authors (MS) has been shown to be effective in reducing problem behaviours and in improving both parenting skills and parental wellbeing [15]. In addition, there is evidence that in depressed mothers Triple P led to reductions in both maternal depression and in problem behaviour in their children [16]. Although there are Triple P studies which have included teenagers, the majority of trials have focussed on parents of pre-teenage children typically aged 2–3 to 9–11 [15].

There is a high demand for both structured psychological interventions for mental health issues [17] as recommended by National Institute for Clinical Excellence [18] and for community based parenting support [19,20]. However many individuals struggle to access either of these types of intervention due to lack of suitably trained therapists. The internet (currently used by 73 % of the UK population [21]) provides an alternative to face to face interventions offering the potential to deliver self-management help flexibly (at the time and location chosen by the client), cheaply and without the stigma that some people feel is associated with seeking support from mental health services [22].

A pilot study by our team has shown that providing simple psychoeducational information on BD along with an early online version of the Triple P Positive Parenting Program led to significant improvements in child behaviour and parenting [23]. The present study builds on this work using a new interactive self-management site for BD developed for the study and integrated with the most recent version of Triple P Online, [24] to provide a web-based integrated bipolar parenting intervention (IBPI).

This paper describes the rationale and protocol for a pilot randomised controlled trial (RCT) of IBPI designed to assess how feasible it is to implement an online parenting intervention for parents with BD. The study will therefore evaluate as primary outcomes, recruitment into the study and consent to participate, retention to the intervention and to follow-up assessments (both arms). The trial will also provide preliminary estimates of the impact of the intervention on child behaviour, parenting skill and confidence, parental mood (including time to further mood episodes) and family functioning.

## Method

This trial is conducted by a multidisciplinary team of researchers, clinicians, service users, and a statistician across academic institutions and NHS Trusts in the United Kingdom. This study was reviewed and approved by the UK NHS Ethics Committee process (REC ref: 12/NW/0749).

### Objective

To determine the feasibility and acceptability of an online integrated parenting intervention for bipolar disorder compared with treatment as usual.

Main research questions:To demonstrate feasibility of recruitment and consenting procedures, adherence to intervention and retention to both arms of the trial across assessment, intervention and 16, 24, 36 and 48 week follow up periods.To provide parameter estimates of clinical outcomes with respect to, child behaviour, parenting skills, mood, and family functioning.

### Trial design

A rater-blind randomised controlled trial which compares sixteen weeks of access to an online integrated bipolar parenting intervention (IBPI) plus treatment as usual (TAU) with TAU alone. The trial is based in the United Kingdom. Randomisation will be carried out by the independent Clinical Trials Unit at The Christie NHS Foundation Trust, Manchester.

### Sample size

The chief purpose of this trial is to evaluate the feasibility and acceptability of providing IBPI, thus a formal power calculation for a test comparing treatment groups is not appropriate.

The primary outcome, to demonstrate feasibility, will be recruitment into the trial and the proportion of completers of the intervention and of assessments at 16, 24, 36 and 48 weeks follow-up. Thirty participants per group, i.e. 60 in total, is sufficient to reliably determine the primary feasibility outcomes for the trial. We therefore aim to recruit N = 100 across both arms of the study to allow for a potential drop-out rate of up to 35-40 % based on an average of attrition rates across 4 relevant studies of web-based interventions for affective and/or parenting issues [20,24-26].

### Recruitment

Participants will be recruited in two ways:Clinician Referral Route

Seventeen National Health Service (NHS) Trusts across the UK are taking part in this study. Community mental health teams, out-patient clinics, GP surgeries, primary care mental health teams and voluntary services will identify potential participants. Care coordinators, research nurses and research development officers will be approached in order to contact potential participants in the first instance. When recruiting in community mental health teams and voluntary services, a member of the research team will present an outline of the study and will provide written material about the study. Potential participants will be offered a participant information sheet by their care co-ordinators or the research team, outlining the study and their role should they wish to take part.2.Self-Referral Routes

The study will be advertised in the media using social networks, such as Facebook, Twitter, relevant online forums and via adverts in local press. Posters and leaflets will be distributed in both NHS and non NHS sites such as relevant third sector bases (i.e. mental health organisations and parenting advice or children’s centres) to maximise participant access. There will be a significant focus on online recruitment. Due to the nature of the study, it is assumed that potential participants seeking advice online are more likely to engage with such an intervention.

Clinicians will be informed of a participant’s involvement in the study subject to participant consent. If a participant does not wish for their primary or secondary care clinician to be informed about their involvement in the study, this does not prevent their participation as long as they consent to their clinician being contacted should they be a significant risk to themselves or others during the study. Figure 1 gives an outline of the participant flow through the study.

**Figure 1 Fig1:**
[figure not shown]
CONSORT diagram showing design of the study

Participants will be asked to express an interest in the study which will act as a ‘run in period’ before consent, so that any potential drop outs occur prior to consent to minimise attrition during the trial [24]. This should also ensure that participants are providing informed consent and are fully committed and motivated to take part in the study before randomisation.

Participants who express an interest in the study, either through self-referral or team referral routes, will be contacted by the IBPI team by telephone to complete a pre-screen form to assess their likely eligibility and be given information regarding the study. If they confirm their wish to participate they will be emailed a participant information pack and web link directing them to consent online. The online link will take the participant to the study website consent screens, each presenting a single clause of the consent form. A consent button is used for each page to ensure there is clear consent to the study as a whole before proceeding to a final screen in which the individual provides their name, email address and telephone number to permit data validation, confirm identity and facilitate contact as required to support assessments. Online registration data will be stored on the secure study database. Once registered, each participant will be provided with login information for both bipolar and parenting modules.

### Inclusion/exclusion criteria

Potential participants must meet the inclusion criteria of:Structured Clinical Interview for DSM-IV Axis I Disorders (SCID) verified diagnosis of bipolar disorder (I, II or Not Otherwise Specified) [27]Have at least one child aged 3 to 10 yearsHave an average of at least 10 h face-to-face contact with this child each weekHave access to the internetSufficient understanding of written and spoken English in order to provide consent, engage with interviews, complete measures and use the intervention

Exclusion criteria:Absence of inclusion criteriaHave a primary diagnosis of alcohol or other substance misuseUnable or unwilling to provide informed consentParent currently receiving an evidence based structured parenting intervention and/or intensive psychotherapyThe index child currently in receipt of intensive structured psychological therapy and/or currently the subject of child protection proceedings

### Outcome measures

To evaluate the feasibility and acceptability of delivering the IBPI intervention the following data will be evaluated: levels of recruitment into the trial; retention of participants in both arms of the study and adherence to and completion of the intervention (website useage).

Structured Clinical Interview for DSM-IV at baseline will be used to confirm bipolar diagnosis and to provide sociodemographic information. Measures of clinical outcome will be recorded at baseline and follow-ups to provide an indication of the effectiveness of the intervention on child behaviour, and parenting skills and confidence. Secondary outcomes are levels of self-reported affective mood symptoms and time to mood episodes and family functioning. All observer-rated follow-up assessments are conducted by telephone, all self-report assessments are completed online.

### Feasibility and acceptability outcomes

The primary outcome of the study is the feasibility and acceptability of IBPI. Feasibility will be measured by recruitment to target and retention to follow-up as well as absence of untoward incidents associated with IBPI. Acceptability will be measured by adherence to intervention through website usage data (pattern and frequency of module access).

### Measurement of primary clinical outcomes

Hypotheses are that IBPI will improve i) Child Behaviour as perceived by the parents and measured by the Strengths and Difficulties Questionnaire (SDQ) [28] and Eyberg Child Behavior Inventory (ECBI) [29]; and ii) Parenting Skills and confidence as measured by the Parenting Scale (PS3) [30], Parenting Sense of Competency Scale (PSOC) [31,32] and Parenting Stress Index (PSI) [33].

### Measurement of secondary outcomes

Hypotheses are that IBPI will improve; i) Self-reported symptoms of mania and depression (Internal States Scale (ISS) [34] Centre for Epidemiologic Studies Depression Scale (CES-D) [35] and the Altman Rating Scale (AMRS) [36]; ii) Observer rated time to relapse and mood symptoms (Structured Clinical Interview for DSM-IV-TR AXIS 1 DISORDERS - LIFE (SCID-LIFE) [37], Hamilton Depression Rating Scale (HAM-D) [38], Bech-Rafaelsen Mania Scale (MAS) [39]; iii) family coherence measured by the Confusion, Hubbub and Order Scale (CHAOS) [40].

### Schedule of assessments

The first follow up assessment occurs 16 weeks from randomisation. See Table 1 for more details on specific assessments and follow up periods. Online assessment measures will be delivered via the LimeSurvey open source questionnaire system (https://www.limesurvey.org/en/). At each online assessment point, participants will be sent an email asking them to follow the link provided to complete the measures. The research team web developer (RP) will monitor the completion of questionnaires and send reminder emails on a regular basis. In the event that email contacts do not elicit a response, the team will make telephone calls to facilitate the completion of measures where such support may be required.

**Table 1 Tab1:** Schedule of assessments

Time point	Type of outcome	Outcome measures	Measuring change in
• Baseline	Feasibility	Recruitment and retention to follow-up	N/A
• 16, 24, 36, 48-weeks post randomization			N/A
• During intervention		Adherence to intervention and website usage	
• 16-weeks post randomization	Acceptability		N/A
• Baseline,	Primary Clinical	SDQ	Child Behaviour
• End of intervention (16 weeks), and		ECBI	Child Behaviour
		PS3	Parenting
• 24-, 36-, and 48- weeks post randomization.		PSOC	Parenting
		PSI	Parenting
Via online survey	Secondary Clinical	ISS	Parent symptoms
		CES-D	Parent symptoms
		AMRS	Parent symptoms
		CHAOS	Parent symptoms
• Baseline,	Secondary Clinical	SCID-LIFE	Parent symptoms
• 24- and 48-weeks post randomization.		HAM-D	Parent symptoms
		MAS	Parent symptoms
Via phone interview with RA			

### Integrated bipolar parenting intervention

An 8 module intervention will be provided to parents offering self-management strategies for bipolar disorder (see Table 2). This is programmed based on the Drupal open source content management system written in PHP with a MySQL database. All modules were developed in partnership with service users with lived experience of bipolar disorder and parenting. The modules listed below cover a range of aspects of living with bipolar disorder all providing a mixture of information, video clips from professionals and service users and self-evaluation exercises. Each module topic is presented in the context of both bipolar disorder and parenting – for instance the ‘benefits and challenges’ module looks at how bipolar mood experiences can have both positive and negative impacts on parenting.

**Table 2 Tab2:** List of IBPI modules

	Bipolar Modules	Triple P Modules
1	What is bipolar disorder?	What is positive parenting?
2	Benefits and challenges	Encouraging desirable behaviour
3	Managing emotions	Teaching new skills and behaviour
4	Knowing yourself	Managing misbehaviour
5	Mood monitoring	Dealing with disobedience
6	Playing to your strengths	Preventing problems by planning ahead
7	Planning for yourself	Making shopping fun
8	Finding support and final thoughts	Raising confident competent kids

After each bipolar module the participant is offered access to the linked parenting module from the Level 4 Triple P online intervention [24]. Both elements of the IBPI intervention share interactive and multimedia features including: video clips, interactive exercises, self-evaluation exercises. Both also share a normalising, self‐regulatory focus to specifically avoid stigmatising or blaming participants.

Each module will typically last around 30 mins and it is anticipated that parents will cover around 1 module per week. Each parent allocated to the intervention arm of the trial has access to the intervention for 16 weeks. Participants are offered modules in the order noted above as they follow logically from one to the next. However, this order of module completion is not obligatory so participants can select modules as they wish and return to those which they find most useful.

### Analysis

#### Feasibility outcomes

The primary purpose of the study is to evaluate the feasibility and acceptability of delivering IBPI therefore a formal power calculation comparing treatment groups is not required. We anticipate that approximately 60 % of subjects will complete the assessment. With 100 subjects recruited across both treatment arms, this proportion will be estimated with 95 % confidence limts +/−9.6 %. The corresponding limits for the estimated proportion within each treatment arm will be +/− 13.6 %

Feasibility is a binary outcome. A simple logistic regression analysis will be used to estimate the probabilities of completion of follow-up in each group at each assessment point, and the differences between the two. Acceptability will be evaluated by analysis of web useage data. Pattern and frequency of module access will be explored through time to access the site from account creation, number of views of each module, order of viewing of modules and number of specific page views.

#### Clinical and functional outcomes

Clinical and functional outcomes consist of repeated measurements. These will be taken at weeks 0, 16, 24, 36 and 48 following randomisation for most measures, except SCID-LIFE, HAM-D and MAS which will be recorded a 0, 24,and 48 weeks (but assessment of episodes covers all the weeks from the previous assessment). Records on participants who drop out of the study before week 48 will be incomplete. Analysis of measurements and dropout times will include checks that groups are balanced with respect to age, gender, level of education and use of services, and control for these as required, followed by linear modelling with correlated errors for the repeated measurements and linked logistic regression models for the probability of dropout conditional on the repeated measurements prior to dropout [41]. In order to inform the design of a definitive trial, these analyses will investigate which patient characteristics affect the repeated measurement outcomes and/or the probability of dropout.

To determine how well IBPI worked for those who did not drop-out, the main clinical outcome measure is D, the difference in SDQ and PS pre- and post-intervention. The corresponding primary analysis will be a two-sample t-test comparing values of D in the two groups. Post-intervention, it is hypothesised that participants who received IBPI will have a greater D than those receiving assessments only. We will also explore website usage data.

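### Covariates for the repeated-measures and dropout models are triggered by observed baseline balance instead of being named in advance, and the t-test on D uses the baseline score only by subtraction

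*Protocol article*

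**What the plan says.** The relevant text is in the protocol article, Analysis, Clinical and functional outcomes. The first step planned there is "checks that groups are balanced with respect to age, gender, level of education and use of services, and control for these as required". The text gives no threshold or test for deciding when control is needed. The covariates so chosen go into two linked models, one for the repeated outcome measurements (linear, with correlated errors) and one for dropout (logistic).

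The outcome data for these models include baseline: "These will be taken at weeks 0, 16, 24, 36 and 48 following randomisation for most measures". The same paragraph adds that "these analyses will investigate which patient characteristics affect the repeated measurement outcomes and/or the probability of dropout", with the aim of informing a definitive trial.

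A separate paragraph deals with participants who do not drop out. There "the main clinical outcome measure is D, the difference in SDQ and PS pre- and post-intervention", and "The corresponding primary analysis will be a two-sample t-test comparing values of D in the two groups". No covariates are attached to that test.

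**The concern.** Randomisation is done by an independent trials unit, so differences between the arms as randomised arise by chance. Observed balance then says little about whether a covariate should be in the model. Its relation to the outcome does. Under the stated rule a strongly prognostic variable that looks balanced can be left out, a weakly prognostic one that looks unbalanced can go in, and the model is settled only after the allocated data have been seen. Because nothing defines when control is needed, two analysts could fit different repeated-measures or dropout models and both be following the text.

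A second weakness lies in the next paragraph. The t-test on D takes account of the baseline score by subtracting it, which is generally less efficient than adjusting for it.

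What is at stake is the quality of the clinical parameter estimates. They are the second of the two main research questions and are meant to inform a later trial. About 60 completers are expected, so precision is scarce.

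**Working it through.** **Inputs from the article.** Recruitment target 100; "We anticipate that approximately 60 % of subjects will complete the assessment"; "Thirty participants per group, i.e. 60 in total, is sufficient to reliably determine the primary feasibility outcomes for the trial". The article's own figures reproduce: 60/(1 − 0.40) = 100; 1.96 × √(0.6 × 0.4/100) = 0.096; 1.96 × √(0.6 × 0.4/50) = 0.136. I therefore use 30 completers per arm below. The article gives no figure for the covariate rule, for the covariates' prognostic strength, or for the correlation ρ between baseline and follow-up scores. Those values are assumptions.

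**1. How often chance triggers adjustment.** Four listed variables, treated as independent, each tested at level α (the article names no test, so α is assumed):
- α = 0.05: 1 − 0.95⁴ = 0.185
- α = 0.10: 1 − 0.90⁴ = 0.344

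These figures show how often the fitted model would change by chance. They measure neither bias nor error.

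**2. What the rule does to the estimate.** Simulation: 30 per arm, four independent normal covariates of equal strength, one complete outcome, no treatment effect, 8,000 runs per setting. The balance rule enters a covariate only if its arm difference has p below the cut-off. The comparator always adjusts for all four.

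| Outcome variance explained by the four | SD of estimate, balance rule (p<0.05) | SD, prespecified | Type I error, balance rule p<0.05 | Type I error, balance rule p<0.10 |
|---|---|---|---|---|
| 0.09 | 0.255 | 0.254 | 5.0% | 4.9% |
| 0.36 | 0.246 | 0.211 | 4.0% | 3.8% |
| 0.64 | 0.234 | 0.157 | 3.2% | 2.4% |

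At 0.36 the variance ratio is (0.246/0.211)² ≈ 1.36. At 0.09 the loss is negligible. A fixed rule does not inflate type I error; it becomes conservative as the covariates become more prognostic.

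If an analyst instead chose the most favourable of the 2⁴ = 16 covariate subsets, simulated type I error (1,500 runs per setting) was about 7–19%. That is the outer bound when no rule is fixed, not what the article describes.

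**3. The t-test on D against analysis of covariance.** Assume equal SDs at both times and in both arms, and work in SD units. The variance of a change score is 2(1 − ρ). The residual variance after adjusting for baseline is 1 − ρ². The relative reduction is 1 − (1 − ρ²)/[2(1 − ρ)] = 1 − (1 + ρ)/2 = (1 − ρ)/2. The 95% half-width is 1.96 × √(2v/30), where v is the variance.

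| ρ (assumed) | v, change | v, adjusted | Reduction | Half-width, change | Half-width, adjusted |
|---|---|---|---|---|---|
| 0.3 | 1.40 | 0.91 | 35% | 0.60 | 0.48 |
| 0.5 | 1.00 | 0.75 | 25% | 0.51 | 0.44 |
| 0.7 | 0.60 | 0.51 | 15% | 0.39 | 0.36 |

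This gain is over the t-test on D. It does not measure the harm done by the balance rule, which governs different models.

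**The case against.** The strongest reply is about scope. The trial's primary outcome is feasibility and acceptability, there is no power calculation for a comparison of arms, and the analysis called primary for the clinical outcome is a t-test without covariates. The balance rule touches none of these. It reaches only the repeated-measures and dropout models of a pilot. This stands, and it limits the weight of the point.

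A reader might infer that the plan leaves out the baseline outcome score. It does not: week 0 is one of the repeated measurements, and D subtracts the baseline. The score is absent only from the list of variables checked for balance. How week 0 enters the longitudinal model is a detail that a condensed article may leave to the full protocol or SAP.

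A reader might also infer that the rule produces false positives. Under a fixed balance test the simulation shows none, and the 7–19% figure requires a free search over subsets that the text does not propose.

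Two further replies have partial force. The article does plan to examine which characteristics affect outcome, but as exploration, and that does not replace the balance trigger. Differences among participants still under observation need not be chance when about 40% may drop out. That is a reason to include predictors of dropout chosen in advance, not to select covariates by how balanced the arms look.

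Finally, an SAP could supply the missing threshold. It would then be making the wrong trigger precise.

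**Conclusion.** The point holds, with modest scope. The article fixes a selection rule that makes the repeated-measures and dropout models depend on chance imbalance, and that rule loses precision compared with covariates named in advance. The size depends on how prognostic the listed variables are, which the documents do not say. In the simulation the loss is almost nil at 9% of variance explained and about 36% in variance at 36% explained. The comparator adjusts for all four variables, so naming one or two recovers only the part that those carry. The simulation uses a single complete outcome, so for the longitudinal model it is a guide only.

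Separately, the t-test on D forgoes a variance reduction of (1 − ρ)/2, or 15–35% for ρ of 0.7–0.3, a range that is assumed.

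The documents do not support a claim that type I error is inflated under a fixed rule, that the baseline score is ignored, or that the feasibility results are affected.

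**What to change.** - Delete balance as a reason for adjustment. Keep the baseline table as description only.
- Name in advance one or two of the four listed variables, chosen as prognostic, and include them in the repeated-measures and dropout models whatever the observed balance.
- Analyse SDQ and PS with the baseline score as a covariate, or as a week 0 response constrained to a common mean in the longitudinal model, in place of the t-test on D.
- Keep the investigation of patient characteristics, labelled exploratory.

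The cost is a sentence or two of text and a few degrees of freedom. With 60 completers a two-sample t-test has 60 − 2 = 58. Adding the baseline score and two single-parameter covariates leaves 60 − 5 = 55, and slightly fewer if education or service use has several categories. No extra data are needed, since the baseline scores are already collected.

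### The clinical analysis labelled primary is a t-test in participants who did not drop out; the repeated-measures model already planned for incomplete records should rank first

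*Protocol article*

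**What the plan says.** The section on clinical and functional outcomes describes two analyses.

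- The first is a linear model with correlated errors for the repeated measurements, linked to logistic models for the probability of dropout given earlier measurements. It is introduced straight after the remark that records of people who leave before week 48 will be incomplete. The section says these analyses are meant to inform the design of a definitive trial.
- The second is introduced with "To determine how well IBPI worked for those who did not drop-out, the main clinical outcome measure is D", where D is the pre- to post-intervention difference in SDQ and PS. It continues: "The corresponding primary analysis will be a two-sample t-test comparing values of D in the two groups". The hypothesis is that "participants who received IBPI will have a greater D than those receiving assessments only".

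On attrition, the sample size section says "Thirty participants per group, i.e. 60 in total, is sufficient to reliably determine the primary feasibility outcomes for the trial", and then "We therefore aim to recruit N = 100 across both arms of the study", "to allow for a potential drop-out rate of up to 35-40" per cent. The feasibility section adds: "We anticipate that approximately 60 % of subjects will complete the assessment".

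Feasibility and acceptability are the trial's overall primary outcome. The clinical results are described as preliminary estimates.

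**The concern.** The protocol fixes three things here: the population (people who did not drop out), the test (an unadjusted t-test of change) and the rank (primary). None of these is left to an unseen analysis plan.

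Not dropping out is a post-randomisation event. The arms differ in ways that could affect it. IBPI parents are offered self-guided modules of about 30 minutes, roughly one a week, while TAU parents have nothing from the trial beyond assessments. If parents who see no improvement leave IBPI more readily than TAU, those who stay will show a benefit that is not there. If the modules drive out families who would have done well, the error goes the other way. The t-test does not even answer its own narrower question cleanly, because TAU stayers are not the counterfactual for IBPI stayers.

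The plan itself treats outcome-related loss as possible, since it models dropout conditional on earlier measurements. Yet the analysis given the primary label is the one more exposed to such loss. At stake is the headline clinical contrast of the pilot, which readers will weigh when judging whether a definitive trial looks promising.

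**Working it through.** **1. The plan's own figures reproduce.**
- Recruitment: 60/(1 - 0.40) = 100, as stated. At 35% drop-out it would be 60/(1 - 0.35) = 92.3, rounded up to 93.
- Overall precision at 60% completion: 1.96 × √(0.6 × 0.4/100) = 0.096. The article gives the same: "this proportion will be estimated with 95 % confidence limts +/−9.6" per cent.
- Per arm: 1.96 × √(0.6 × 0.4/50) = 0.136, matching the stated 13.6%. This implies 50 per arm, although the allocation ratio is not stated.

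**2. How many would enter the t-test.** At 35-40% drop-out, 60-65 of 100 would be analysed (30 to about 33 per arm) and 35-40 left out. The rate is an upper allowance and is not tied to week 16, the only follow-up that D needs. The number left out of the t-test could be smaller.

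**3. Possible bias with a true effect of zero.** Put D on a scale with SD 1. Suppose a participant stays when a normal latent variable, correlated r with D, exceeds a threshold that leaves a proportion p in the arm. The mean of D among stayers is then r × φ(c)/p, with c = z(1 - p). The bias in the difference between arms is

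r × [φ(c₁)/p₁ - φ(c₀)/p₀].

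The values of φ(c)/p are 0.798 at p = 0.50, 0.497 at 0.70, 0.880 at 0.45 and 0.424 at 0.75.

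| Completion, IBPI v TAU (average 60%) | r = 0.3 | r = 0.5 |
|---|---|---|
| 50% v 70% | 0.3 × 0.301 = 0.09 SD | 0.5 × 0.301 = 0.15 SD |
| 45% v 75% | 0.3 × 0.456 = 0.14 SD | 0.5 × 0.456 = 0.23 SD |
| 60% v 60%, same r in both arms | 0 | 0 |

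The arm splits and r are assumptions; only the 60% average comes from the article.

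A separate simulation let staying depend on D through a logistic model (log-odds 0.5 or 1.0 per SD). It gave 0.09 and 0.16 SD at 50% v 70%, and zero at equal 60% with the same dependence in both arms. With equal 60% completion but dependence on D only in the IBPI arm (log-odds 0.25, 0.5, 1.0), it gave 0.10, 0.19 and 0.33 SD.

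**4. Scale.** With 30 per arm the standard error of the difference is √(2/30) = 0.26 SD. A bias of 0.2 SD would raise the two-sided 5% error rate to about 12%.

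**5. What the repeated-measures model would recover.** Week 16 is the first follow-up, so anyone lost for good before it contributes only a baseline value. Suppose loss depends on improvement itself, as in step 3, and the baseline to week-16 correlation ρ is 0.5 or 0.7 (assumed). To a close approximation the model keeps a fraction (1 + ρ)/2 of the t-test's bias: 0.75 at ρ = 0.5 and 0.85 at ρ = 0.7. A simulation of the same scenarios gave 0.07-0.13 SD where the t-test gives 0.09-0.15, and 0.10-0.20 where it gives 0.14-0.23. About 13-25% of the bias is removed. The gain is larger if loss depends on measured values rather than on unobserved improvement.

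**The case against.** The strongest reply is that little is wrong. The longitudinal model is already planned and described first. The t-test is openly presented as a narrower question, so the dispute is over which of two planned analyses carries one label. The trial is a feasibility pilot, and no feasibility conclusion depends on that label. The bias is hypothetical, below one standard error in the step 3 table, and zero if loss acts alike in both arms. The model would not remove it where loss depends on unobserved improvement. All of this stands, and it lowers the severity. It does not justify giving the primary label to the comparison with less protection.

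Four stronger readings are tempting but not supported:

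- *A reader might infer that the planning effect size for the definitive trial comes from the t-test.* The article attaches informing the definitive design to the longitudinal and dropout models. The abstract speaks of effect sizes from measures at all five time points.
- *A reader might infer that the t-test discards week-16 values of people who leave later.* The mention of week 48 describes incomplete longitudinal records. No rule says the t-test drops anyone who has baseline and week-16 values, though the wording leaves this open.
- *A reader might take the reference to those who received IBPI as an as-treated comparison.* The test compares the two groups, and no exposure rule is given.
- *A reader might state that 40 of 100 will be excluded.* The article gives an upper allowance, not a week-16 forecast.

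**Conclusion.** The point holds as one of ranking and labelling. The clinical analysis named primary conditions on staying in the trial, with substantial drop-out allowed for, so its contrast is not a randomised comparison and may be biased in either direction.

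The size cannot be known from the article. The range of 0.09-0.23 SD rests entirely on assumed unequal completion and an assumed correlation of 0.3-0.5 between staying and improving. Promoting the longitudinal model is the better choice because it keeps everyone as allocated and uses incomplete records. It still relies on loss being explained by observed data and only partly reduces bias from people lost before week 16. Severity: should-fix.

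**What to change.** 1. Name the planned repeated-measures model as the main clinical analysis for SDQ and PS. Include all randomised participants as allocated, with baseline as one of the repeated measurements, and report the IBPI minus TAU contrast at week 16 with a 95% CI.
2. Keep the t-test of D as a labelled supportive analysis, in everyone with baseline and week-16 values whether or not they leave later.
3. In the hypothesis, refer to participants allocated to IBPI rather than those who received it.
4. State that the model assumes loss is explained by observed data, and that people lost before week 16 contribute baseline data only, so bias is reduced rather than removed.

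The cost is wording only: the model is already planned and no further data are needed. The change should be made before outcome data are analysed, so that the ranking is not chosen with results in view.
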